#### Hypothesis

Prosthetic rehabilitation of edentulous patients will reduce pain symptoms of TMD as compared to patients without rehabilitation.

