### Interventions

The participants will be grouped into 3 interventional and 3 control groups based on their state of edentulism (Figure 1; higher-resolution version in Multimedia Appendix 1). The interventional groups are:

Partially edentulous arch—Kennedy Class I and Class II: Kennedy Class I describes a patient who has edentulous areas bilaterally, posterior to the remaining natural teeth. Kennedy Class II describes a patient who has a one-sided edentulous area, posterior to the remaining natural teeth. The participants of this group will receive mouth preparation, prosthetic rehabilitation with removable partial denture, and comprehensive counseling (n=50).Partially edentulous arch—Kennedy Class III and Class IV: In Class III the edentulous area has teeth located both anteriorly and posteriorly to it. In Class IV, there will be a single but bilateral (crossing the midline) edentulous area located to the anterior of the remaining natural teeth. The participants of this group will receive mouth preparation and prosthetic rehabilitation with removable partial denture followed by management with stabilization splint and comprehensive counseling (n=50).Completely edentulous arches: The participants of this group will receive prosthetic rehabilitation with removable complete denture and comprehensive counseling (n=50).

Each of the 3 mentioned interventional groups will have their corresponding control groups with 50 participants in each control group. The participants in all the 3 control groups will receive symptomatic treatment and comprehensive counseling.

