### Sequence Generation

The selected patient for trial will be randomly allocated to either the intervention arm or the control arm of their group, as per computer-generated randomization, schedule stratified, based on the type of group it belongs. The selected individuals will be allocated in equal probabilities to the intervention and control groups by stratified randomization. Stratified randomization is achieved by performing a separate randomization procedure within each of the two strata of participants. This will ensure that the numbers of participants receiving each intervention are closely balanced within each stratum. Treatment assignments are then made from separate randomization lists created in advance of the trial for each stratum.

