### Statistical Methods

The effectiveness of pain reduction within each arm and between each group will be analyzed using analysis of variance. The details of the analysis are explained in Table 3.

**Table 3 table3:** List of proposed analysis for trial results.^a^

Variable/outcome			Hypothesis		Outcome measure		Methods of analysis
Effectiveness of reduction of pain: within each arm			Intervention improved outcome from baseline to 12 months		Per person reduction of VAS^b^ score and GCPS^c^ (proportion or mean)		Chi-square methods or ANOVA^d^
Effectiveness of reduction of pain: between group 1, group 2, and group 3			Intervention improved outcome from baseline to 12 months		Per person reduction of VAS score and GCPS (proportion or mean)		Chi-square methods or ANOVA

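### No main row of Table 3 compares intervention with control on pain: the rows listed are change within arms and a comparison of non-randomised edentulism groups

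*Protocol article*

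**What the plan says.** The Hypothesis section states a between-treatment claim: "Prosthetic rehabilitation of edentulous patients will reduce pain symptoms of TMD as compared to patients without rehabilitation". Sequence Generation randomises on that contrast. Patients are "randomly allocated to either the intervention arm or the control arm of their group", and "The selected individuals will be allocated in equal probabilities to the intervention and control groups by stratified randomization".

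Groups 1, 2 and 3 are something else. Under Interventions, "The participants will be grouped into 3 interventional and 3 control groups based on their state of edentulism": Kennedy Class I and II, Kennedy Class III and IV, and complete edentulism. Table 2 gives each group 50 intervention and 50 control patients.

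Statistical Methods says "The effectiveness of pain reduction within each arm and between each group will be analyzed using analysis of variance" and refers to Table 3 for details. The main rows of Table 3 are the reduction in pain within each arm and "Effectiveness of reduction of pain: between group 1, group 2, and group 3". Both carry a hypothesis of improvement from baseline to 12 months, and both give the method as "Chi-square methods or ANOVA". The subgroup rows are groups 1 to 3 again (a regression with an interaction whose terms are not named), posterior versus anterior teeth, upper versus lower teeth, duration of edentulism, and number of quadrants.

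**The concern.** The article does not leave the choice of contrast open. It lists the proposed analyses, and the comparison that randomisation was set up to support is not among the main ones. Someone following the list would report whether patients improved from baseline and whether the three edentulism types differed, and could finish without testing the trial's hypothesis.

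Both listed main analyses can mislead. Patients in either arm may improve because both arms receive counselling, because symptoms fluctuate, or because entry through a positive pain screener is followed by regression to the mean. Differences between groups 1, 2 and 3 reflect type of tooth loss, type of denture and, in group 2, the splint. Neither isolates the prosthesis.

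**Working it through.** **1. Contrasts side by side**

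| Item | Contrast | Randomised? |
|---|---|---|
| Hypothesis | rehabilitated v not rehabilitated | yes |
| Sequence Generation | intervention v control, within group | yes |
| Table 3, main row 1 | baseline v follow-up, within each arm | no |
| Table 3, main row 2 | group 1 v 2 v 3 | no |
| Table 3, first subgroup row | group 1 v 2 v 3, regression with unnamed interaction | unclear |
| Table 3, other subgroup rows | tooth position, arch, duration, quadrants | no |

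**2. The plan's own figure.** Sample Size gives effect size 0.77 (for EMG activity), alpha 0.05, power 80% and 22 per group. A two-sample t-test reproduces 22 if one-sided (21.6, rounded up) and gives 28 if two-sided (27.5, rounded up). So the size was derived for a comparison of two groups. The sidedness is a separate matter. Below, 0.77 SD is borrowed as an illustrative effect on pain.

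**3. Can the group comparison detect a prosthesis effect?** Assumptions: SD 1, 50 intervention and 50 control patients per group, a true benefit of 0.77 SD equal in all groups, two-sided 0.05, 10,000 simulated trials.
- ANOVA of groups 1, 2 and 3, intervention patients only: significant in 5.1%.
- The same with both arms pooled in each group: 3.2%.
- Intervention v control: practically 100%.

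The 3.2% can be checked by hand. An equal benefit leaves the three group means equal, but pooling the arms raises the within-group variance from 1 to about 1 + 0.77²/4 = 1.15. The 5% critical value of F(2, 297), 3.03, then acts like 3.03 × 1.15 = 3.48, which F exceeds with probability 0.032.

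**4. Can within-arm change stand in?** Suppose the prosthesis has no effect and both arms improve equally. The documents give no size for this, so a range is assumed: entry 0.5 to 1.0 SD above the population mean, and baseline-to-follow-up correlation ρ of 0.5 to 0.7. Expected improvement is (1 − ρ) × excess. Dividing by √(2(1 − ρ)) puts it in SDs of the change.

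| Excess | ρ | Improvement (SD) | In SDs of change | Paired t significant, n = 50 | n = 150 |
|---|---|---|---|---|---|
| 0.5 | 0.7 | 0.15 | 0.19 | 27% | 65% |
| 0.5 | 0.5 | 0.25 | 0.25 | 41% | 86% |
| 1.0 | 0.7 | 0.30 | 0.39 | 77% | 99.7% |
| 1.0 | 0.5 | 0.50 | 0.50 | 93% | 100% |

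For the last line, simulation of intervention v control gives 4.9%, the nominal error rate.

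**5. What the missing comparison would deliver.** Detectable difference at 80% power, two-sided 0.05: (1.96 + 0.84) × √(2/n).
- n = 150 per arm: 2.80 × 0.1155 = 0.32 SD.
- n = 50 per arm, one group: 2.80 × 0.2 = 0.56 SD.
- n = 47 per arm (5% loss): 2.80 × 0.206 = 0.58 SD.

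**The case against.** **Vocabulary.** The article uses arm and group loosely. Sequence Generation itself speaks of patients "allocated in equal probabilities to the intervention and control groups by stratified randomization", Sample Size refers to an interventional and a control group, and Patient Selection allocates to arms by dental state. The sentence on analysis between each group might therefore have meant intervention against control. The looseness is real, but that sentence defers to Table 3, which names groups 1, 2 and 3.

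**The subgroup regression.** A treatment-by-group interaction needs a treatment term and the controls, so a treatment coefficient is probably estimated there. That stands, and it rules out saying that Table 3 contains nothing of the randomised contrast. But the terms are unnamed, the row is labelled subgroup, and an interaction asks whether effects differ, not whether the prosthesis works.

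**Stronger readings that a reader might infer.**
- That the 150 controls contribute nothing. The documents do not support this: within-arm rows cover control arms, Table 2 counts controls inside each group, and the interaction model would use them. What is missing is an explicit contrast of controls with treated patients.
- That offering a proportion or a mean, with "Chi-square methods or ANOVA", lets the test be picked after seeing the data. The same cell covers the VAS, a 0 to 100 score, and the Graded Chronic Pain Scale, graded 0 to IV. The alternatives may simply match outcome type.
- That the percentages in step 4 forecast this trial. Recruitment is from routine dental care by screener, with no VAS threshold for entry, so the size of regression to the mean is unknown. The formula applies to excess over the population mean, not over a patient's own usual pain.

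**Covariates.** An unadjusted arm comparison of change would also be valid under randomisation, and covariates are often left to an analysis plan. Baseline adjustment is a gain in precision and forms no part of the defect.

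**Conclusion.** The point holds. No main row of Table 3 states the intervention-versus-control comparison that the hypothesis and the randomisation call for, and the two main rows cannot replace it. The core conclusion follows from reading the sections together and needs no numerical assumption. The 5.1% and 3.2% figures assume a benefit equal in all three groups. If the benefit differed by group, the group test would gain power, but for that difference and not for the effect of the prosthesis. The 27% to 100% range for within-arm tests is illustrative only.

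This must be fixed before analysis, because the list as written could be carried out in full without a stated primary test of the hypothesis. It is a fault in the written list; the documents do not show a decision to leave the comparison out.

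**What to change.** Insert a first row in Table 3: VAS pain (mm), intervention versus control; linear model with arm, baseline VAS and group 1/2/3 stratum; adjusted mean difference with 95% CI at the primary time point. Fill in that time point only after reconciling the 3-month outcome schedule with the 12-month wording in Table 3. Name the arm-by-group interaction as a secondary analysis, with its terms written out. Label the within-arm and group 1 v 2 v 3 rows descriptive. Use arm for intervention or control and group for edentulism type throughout.

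The analysis population rule under Analysis Population and Missing Data is a separate issue, which this row does not settle.

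Cost: rewriting one table and one sentence. Baseline VAS and group are already collected, and the sample size does not change.

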**Subgroup analysis**							
	Effectiveness of reduction of pain: between group 1, group 2, and group 3	Intervention improved outcome from baseline to 12 months		Per person reduction of VAS score and GCPS (proportion or mean)		Regression methods with appropriate interaction term	
	Between posterior teeth rehabilitation vs anterior teeth rehabilitation	Number of teeth affects effectiveness of outcome		Per person reduction of VAS score and GCPS (proportion or mean)		Chi-square methods	
	Upper vs lower teeth	Position of edentulism affects the effectiveness outcome		Per person reduction of VAS score and GCPS (proportion or mean)		Chi-square methods	
	Duration of edentulism	Duration of edentulism affects pain outcome		Per person reduction of VAS score and GCPS (proportion or mean)		Chi-square methods	
	Number of quadrants	Number of quadrants affects the effectiveness outcome		Per person reduction of VAS score and GCPS (proportion or mean)		Chi-square methods	

^a^In all analyses, results will be expressed as coefficient, SEs, corresponding 95%, and associated *P* values. Goodness of fit will be assessed by examining the residuals for model assumptions and chi-square tests for goodness of fit.

^b^VAS: visual analog scale.

^c^GCPS: Graded Chronic Pain Scale.

^d^ANOVA: analysis of variance.

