### Sample Size

The activity of masticatory muscle (mean and SD) while chewing, estimated by EMG, reflects the TMD in a patient [35]. With a power of 80%, alpha error of .05, and effect size of 0.77, the minimum sample size estimated for each group was 22. Considering attrition and the inclusion of various variables (edentulousness location, etc), we increased the sample to 50 for each interventional group. The sample size of 50 will have a minimum of 20 patients with edentulous maxilla and 20 patients with edentulous mandible for intervention groups 1 and 2. The total sample size for the study is 300 with 150 for the interventional group and 150 for the control group. Please refer to Table 2 for the sample breakdown.

**Table 2 table2:** Sample size breakdown.

			Group 1: removable partial denture, n		Group 2: removable partial denture with stabilization splint, n		Group 3: removable complete denture, n		Total, n
**Intervention**			50		50		50		150
	Patients with edentulous maxilla	20		20		20			
	Patients with edentulous mandible	20		20		20			
	Total	40		40		40			
	Females	20		20		20			
	Males	20		20		20			
	Total	40		40		40			
**Control**			50		50		50		150
	Patients with edentulous maxilla	20		20		20			
	Patients with edentulous mandible	20		20		20			
	Total	40		40		40			
	Females	20		20		20			
	Males	20		20		20			
	Total	40		40		40			
Sample per group			100		100		100		300

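### The posterior-versus-anterior subgroup row is defined by treatment received, so read literally it is an uncontrolled contrast, partly tied to splint use, that cannot show whether region changes the effect of rehabilitation

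*Protocol article*

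**What the plan says.** The subgroup part of Table 3 (Protocol article, Statistical Methods) contains the row "Between posterior teeth rehabilitation vs anterior teeth rehabilitation". Its hypothesis is "Number of teeth affects effectiveness of outcome", its outcome is the per-person reduction in VAS and Graded Chronic Pain Scale scores, and its method is chi-square. The next row, on upper against lower teeth, has the hypothesis "Position of edentulism affects the effectiveness outcome", which is a baseline feature. The first subgroup row, on groups 1 to 3, is the only one to name regression with an interaction term.

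The Interventions section fixes who receives what:
- Controls: "The participants in all the 3 control groups will receive symptomatic treatment and comprehensive counseling".
- Group 3 intervention: "The participants of this group will receive prosthetic rehabilitation with removable complete denture and comprehensive counseling".
- Group 1 (Kennedy I and II) receives a removable partial denture.
- Group 2 (Kennedy III and IV) receives a removable partial denture followed by a stabilization splint.

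On numbers, the Interventions section states "Each of the 3 mentioned interventional groups will have their corresponding control groups with 50 participants in each control group", and Sample Size states "The total sample size for the study is 300 with 150 for the interventional group and 150 for the control group".

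**The concern.** A subgroup analysis in a randomised trial asks whether the difference between arms varies with a characteristic that patients in both arms have before allocation. The region of the teeth rehabilitated is not such a characteristic, because it exists only for patients who received a prosthesis. A comparison within the treated set shows which patients improved more. It cannot separate a regional difference in treatment effect from a regional difference in natural course or in response to counseling.

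The row belongs to the protocol's secondary objective, which concerns characteristics of edentulism such as Kennedy class. Followed as written, it could yield a statement that rehabilitation works better in one region when the analysis contains no unrehabilitated patient. The mismatched hypothesis adds to the problem, since neither number of teeth nor region is clearly the question.

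**Working it through.** **1. Planned numbers.** Six cells of 50 (three groups, two arms): 6 × 50 = 300, split 150 and 150. This reproduces the stated total.

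**2. Who has a value on the factor as worded.**
- Controls: 3 × 50 = 150, no prosthesis, no value.
- Group 3 intervention: 50. A complete denture replaces anterior and posterior teeth together, so neither level applies.
- Remaining: 300 − 150 − 50 = 100, the intervention patients of groups 1 and 2. Any of these with both regions restored would also fit neither level; the article gives no count.

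**3. What separates the two levels among those 100.** Interventions defines Kennedy I and II by edentulous areas behind the remaining teeth, so every group 1 patient has a posterior area. Kennedy IV, in group 2, is anterior. Anterior-only cases can therefore arise only in group 2, where the splint is given. The posterior level draws on group 1 (no splint) and possibly part of group 2 (splint), while the anterior level is all splint. Region and splint use are partly the same variable.

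**4. Precision of the treated-only contrast.** The anterior count is not given. Assume 10 to 50 anterior patients of the 100, with two-sided alpha of .05 and 80% power. The detectable standardised difference is about (1.96 + 0.84) × √(1/a + 1/(100 − a)):
- a = 10: 2.80 × 0.333 = 0.93 (0.94 by the t-test calculation)
- a = 50: 2.80 × 0.200 = 0.56 (0.57 by the t-test calculation)

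These values describe a non-randomised difference, so even good precision would not answer the question.

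**5. The same question on baseline region.** Kennedy class is known in both arms before allocation, and Sequence Generation randomises within group. Groups 1 and 2 then contribute 4 × 50 = 200 of 300. Group 3, both arms, is outside: 100 of 300 (33.3%).

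**6. Precision of the interaction.** Once group and arm-by-group terms are in the model, the anterior-only against posterior-only interaction is informed essentially by group 2. Assume 10 to 25 anterior-only patients per arm of 50, the rest posterior-only, equal numbers by arm, a common SD and no losses. The detectable difference between the two treatment effects, in SD units, is about 2.80 × √(2/a + 2/(50 − a)):
- a = 10: 2.80 × √(0.20 + 0.05) = 2.80 × 0.50 = 1.40
- a = 25: 2.80 × √(0.08 + 0.08) = 2.80 × 0.40 = 1.12

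Only a very large regional difference would be detected. This supports an exploratory label.

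**The case against.** The strongest reply is that the label is only loose. Groups are formed by edentulous state in both arms, the neighbouring row speaks of the position of edentulism, and every group 1 control has a posterior edentulous area by definition. On that reading, the 100 controls of groups 1 and 2 are easily placed. Alternatively, the row may be meant as a comparison among treated patients, in which case controls are left out on purpose. Coding details, such as a level for both regions, are commonly left to a fuller document.

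Much of this stands. A reader might infer from the row that 150 + 50 = 200 of 300 patients (66.7%) cannot be analysed. The article does not support that: baseline region is available for the partially edentulous controls, and under a treated-only reading controls are not lost but simply not part of the comparison.

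A reader might also extend the point to the upper-against-lower row. That row already rests on a baseline feature that both arms have. Table 2 plans 20 edentulous-maxilla and 20 edentulous-mandible patients in each cell of 50 and gives no count for both arches, so no gap of known size can be shown there.

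The replies do not rescue the row as written. If it is treated-only, it is non-randomised and mixed with splint use. If it is meant on baseline region, the stated factor is wrong, a chi-square test without an interaction still does not compare treatment effects, and the stated hypothesis still concerns something else. The point is therefore about what the table fixes, not about detail left to another document.

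**Conclusion.** The point holds in limited form. Taken literally, the row is a chi-square contrast among at most 100 of 300 patients, all treated, in which anterior-only cases occur only in the splint group. It cannot show whether the effect of rehabilitation depends on region, and its hypothesis does not match its contrast. The counts rest on the planned cell sizes and on a complete denture covering both regions. The precision figures rest on assumed anterior counts, because the article gives none. Only one subgroup row is affected; the randomisation, the sample size and the primary comparison are not. This is a minor point.

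**What to change.** Change the row in Table 3 as follows:
- **Factor:** baseline region of edentulism, with levels posterior only, anterior only and both, taken from the visit 1 oral examination in both arms and recorded before the randomisation code is opened.
- **Population:** groups 1 and 2, both arms (200 patients planned), stating that group 3 is excluded because complete edentulism has no regional level.
- **Method:** in place of chi-square, a regression with an arm-by-region interaction that also includes group (1 or 2) and its interaction with arm; or the same test within group 2 alone. Within group 2 the splint is part of the intervention for every region, so the interaction concerns denture and splint together.
- **Hypothesis:** the effect of rehabilitation on pain reduction differs by baseline region. Number of teeth, if still of interest, needs its own row.
- **Status:** exploratory, with the stated reason that region is partly tied to splint use.

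The cost is wording. Table 1 already schedules the oral examination at visit 1, and Allocation Concealment Mechanism already requires baseline measurements before the code is released. The downsides are that group 3 lies outside this subgroup and that the interaction will be imprecise.

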#### Secondary Objective

The secondary objective is to determine the effect of the span of edentulism, the number of quadrants involved, pathological migration, the type of Kennedy classification, and the prosthetic status on temporomandibular joint dysfunction signs and symptoms.

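### Three subgroup rows in Table 3 claim that a factor changes effectiveness but name only chi-square methods, with no arm or interaction term

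*Protocol article*

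**What the plan says.** The subgroup block of Table 3 (Statistical Methods) has five rows. All take as outcome each person's reduction in VAS and GCPS, as a proportion or a mean.

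- Group 1 v 2 v 3: "Regression methods with appropriate interaction term".
- Posterior v anterior rehabilitation: hypothesis "Number of teeth affects effectiveness of outcome"; method "Chi-square methods".
- Upper v lower teeth: hypothesis "Position of edentulism affects the effectiveness outcome"; same method.
- Duration of edentulism: hypothesis "Duration of edentulism affects pain outcome"; same method.
- Number of quadrants: hypothesis "Number of quadrants affects the effectiveness outcome"; same method.

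Footnote a to the table says that every analysis will be reported with coefficients and standard errors. None of the four chi-square rows mentions the randomised arm or an interaction.

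**The concern.** Whether a factor affects effectiveness is a question about a difference between differences: prosthesis v control at one level of the factor, against prosthesis v control at the other. A cross-tabulation of response by factor does not contain that contrast. Pooled over arms, it tests whether the factor goes with improvement whatever the treatment. Within the intervention arms alone, it mixes prognosis with any change in the treatment effect, because nothing shows how similar control patients fared.

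The error can run both ways. A factor that is only prognostic may be reported as changing what the prosthesis achieves, and a true change in effect may be missed. Two smaller defects sit in the same rows. A plain chi-square test yields no coefficient or standard error, contrary to footnote a. The posterior/anterior row compares tooth location but states its hypothesis about the number of teeth.

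**Working it through.** The plan gives no figure for the subgroup tests, so there is none to reproduce.

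**Inputs.** Table 2 lists 20 patients with an edentulous maxilla and 20 with an edentulous mandible in each arm of each group. Over three groups and two arms that is 20 × 6 = 120 v 120; in the intervention arms alone, 20 × 3 = 60 v 60. The Sample Size text sets the 20/20 minimum only for intervention groups 1 and 2. Using groups 1 and 2 only gives 80 v 80 pooled and 40 v 40 in the intervention arms. Response rates are not in the plan and are assumptions here.

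**Step 1: rejection rate when the factor is only prognostic.** Rates by jaw are the same in both arms, so the treatment effect does not differ by jaw. Effect size h = 2·asin√p₁ − 2·asin√p₂; power ≈ Φ(h·√(n/2) − 1.96), with n per jaw.

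- 60% v 40%: h = 0.403. For n = 120: 0.403 × √60 = 3.12, and Φ(1.16) = 0.88. For n = 60: 0.403 × √30 = 2.21, and Φ(0.25) = 0.60.
- 55% v 45%: h = 0.200. For n = 120: Φ(1.55 − 1.96) = 0.34. For n = 60: Φ(1.10 − 1.96) = 0.19.

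| Patients per jaw | 60% v 40% | 55% v 45% |
|---|---|---|
| 120 v 120, pooled, all groups | 88% | 34% |
| 80 v 80, pooled, groups 1 and 2 | 72% | 24% |
| 60 v 60, intervention arms, all groups | 60% | 19% |
| 40 v 40, intervention arms, groups 1 and 2 | 44% | 15% |

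A valid interaction test rejects in about 5% throughout.

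**Step 2: simulation with a real treatment effect (20,000 runs).** Assumed rates are intervention/control. The interaction test is a Wald test on the difference of risk differences. Cells are arm by jaw: 20 per cell is one group, 60 is all three.

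| Scenario | Per cell | Pooled chi-square | Intervention-arm chi-square | Interaction test |
|---|---|---|---|---|
| Prognostic only: upper .70/.50, lower .40/.20 | 20 | 80% | 46% | 6% |
| | 60 | 99.8% | 92% | 5% |
| True interaction: upper .70/.30, lower .50/.50 | 20 | 5% | 24% | 46% |
| | 60 | 4% | 61% | 90% |
| True interaction: upper .60/.20, lower .60/.60 | 20 | 45% | 5% | 48% |
| | 60 | 88% | 5% | 91% |

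In the last two scenarios the treatment effect is 40 points in one jaw and zero in the other. One form of the chi-square stays at about its 5% level in each.

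**Step 3: what a proper interaction test can detect on a continuous outcome.** The standard error of the interaction is √(4/n) SD with n per cell, and 80% power at two-sided 5% needs 2.80 standard errors.

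- n = 20: 2.80 × 0.447 = 1.25 SD.
- n = 40 (groups 1 and 2 pooled): 2.80 × 0.316 = 0.89 SD.
- n = 60: 2.80 × 0.258 = 0.72 SD.

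**The case against.** The strongest reply is that the table names a family of methods in a condensed list. It does not say what is cross-tabulated or that arms are pooled, and the promise of coefficients suggests a model behind the shorthand. A stratified or homogeneity test by arm could fall under the same label. It is true that pooling is not stated, which is why both readings are computed above. But no such test is named, the row directly above names its interaction term, and both plain readings fail. The table fixes a method for these rows, so this is not detail left to an analysis plan.

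Second, a reader might infer that all four chi-square rows are wrong. The documents do not support that. The duration row speaks of an effect on pain, and a test without the arm can answer that literal question. The Secondary Objective likewise asks about "the effect of the span of edentulism, the number of quadrants involved, pathological migration" and other factors in relation to joint signs and symptoms, which is association wording. It gives no support for reading every row as effect modification.

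Third, a reader might split all 300 patients 150 v 150 by jaw, which gives 94% and 41%. Table 2 assigns only 40 of each 50 to a jaw, so 120 v 120 is the most it supports.

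Fourth, a chi-square forces VAS reduction into categories, and one might price that loss as for a median split. The plan names no cut for the reduction, and the GCPS is an ordered grade to begin with, so no such figure is claimed.

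Finally, one might fear that a false subgroup finding would pass directly into treatment guidance. The article's Conclusions say only that the data will help develop treatment protocols, and the primary comparison is untouched.

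**Conclusion.** The concern holds for three rows: posterior v anterior, upper v lower, and number of quadrants. Each states a hypothesis about effectiveness and fixes a method that, as named, cannot test it or deliver the reporting in footnote a. For a purely prognostic jaw factor, the chance of a significant chi-square is about 34% to 88% with arms pooled at Table 2 counts and about 19% to 60% in the intervention arms alone, against about 5% for a valid interaction test. With groups 1 and 2 only, the range is 15% to 72%. These figures rest on assumed response rates. The qualitative conclusion does not depend on those values, only on the factor having some prognostic value. The duration row is an ambiguity of label, not a wrong test. The matter is confined to subgroup analyses and should be corrected before analysis.

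**What to change.** For the three rows, replace the chi-square entry with a regression of the outcome on arm, factor and arm × factor, adjusted for the baseline value and the randomisation stratum: linear for VAS, ordinal or logistic for GCPS grade.

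- Restrict each model to the groups in which the factor varies. Completely edentulous patients have no posterior/anterior contrast, and jaw and quadrants may not vary among them.
- Use the final time point once the timing is reconciled: the Outcomes section ends measurement at 3 months, while other rows of Table 3 refer to 12 months.
- Report the interaction with its 95% confidence interval and label it exploratory, in view of the detectable sizes above.
- Duration row: either label it a prognostic association or use the same interaction model, keeping duration numeric.
- Posterior/anterior row: state the hypothesis about location, and give number of teeth its own row.

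The cost is rewriting the table rows and a little more analysis. Arm, factor and outcome data are already planned, so no new data are needed.
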